### Intervention

Participants in both groups will be provided with calcipotriol betamethasone ointment. Subjects randomized to the experimental group will receive integrated auricular acupressure therapy and calcipotriol betamethasone ointment topical therapy.

### Auricular acupressure treatment

Patients in the auricular acupressure plus calcipotriol betamethasone ointment group will receive auricular acupressure treatment once a week for 4 weeks. At every visit, therapists treat the patients with auricular acupressure. All of the therapists participated in this trial will be standardized in their training, including in the study protocol and methods of treatment. We selected auricular acupoints as suggested in the nomenclature and location of auricular points [33]. The auricular acupoints are based on a set of anatomical maps superimposed onto the ear. The following auricular points will be used for treatment: Lung (Fei, CO14), Shenmen (TF4), endocrine (CO18), Subcortex (AT4) and Liver (Gan, CO12) (Fig. 1). According to modern research and Chinese medicine, ‘The liver (Gan) stores blood. Liver dispersion, *qi* stagnation’, ‘The lung (Fei) governs skin and hair’, and, in addition to treating respiratory-related disease, the auricular points Liver (CO12) and Shenmen (TF4) work on regulating emotion and reducing stress, anxiety, and excessive sensitivity [34, 35]. Lung (CO14) also works on relieving painful and itchy skin diseases [36]. Endocrine (CO18) and Pizhixia (AT4) could be helpful with endocrine hormone balance, hypersensitivity, and rheumatism [37, 38].

After sterilization with 75% alcohol, *Vaccaria* seeds will be stuck and fixed on the above auricular points of both ears, with each pressed individually for 1 min to induce stimulus until patients feel endurable heat and distending pain on the auricles, and patients are advised to repeat the pressing themselves four times daily for 5 consecutive days and then to remove the seeds stuck to their auricles on the morning of day 6, which is helpful to avoid contact dermatitis caused by long-term adhesive tape.

### Calcipotriol betamethasone ointment treatment

Traditional topical therapies (such as corticosteroids, vitamin D and analogues, dithranol, and tar preparations) are recommend by NICE guideline as first-line therapy [39]. In this study, we used a routine drug for first-line therapy in the control group and as a base treatment in the intervention group. Thus, participants in both groups will be provided with calcipotriol betamethasone ointment (Daivobet® gel; calcipotriol 50 μg/g plus betamethasone 0.5 mg/g) for topical use once daily until the PASI score of the patient is reduced to 0. However, the course of calcipotriol betamethasone ointment treatment would last no more than 4 weeks.

### Outcome

#### Primary outcome measurement

The primary outcome measure in the trial is relapse rate in the treatment period and follow-up period. Relapse is defined as losing 50% of the improvement obtained from treatment once the treatment is stopped [40]. The PASI will be assessed every visit during the treatment period and the follow-up period. Meanwhile, patients will be required to report the emergence of a variety of conditions at any time in the study period. Assessors will evaluate the PASI score on the same or closest day. Target lesions will be recorded as digital photographs by single-lens reflex (SLR) cameras at every visit.

#### Secondary outcome measurements

Secondary outcome measures include the time to relapse, rebound rate, time to new onset, PASI improvement rate, BSA affected, a visual analog scale (VAS), and Dermatology Life Quality Index (DLQI). Time to relapse is defined as the time it takes to lose 50% of the improvement obtained from treatment (Table 1). Time to new onset is the PASI score improvement achieved (PASI-50) for the first time, but a failure to keep the PASI-50 improvement all through the treatment period. Rebound is defined as a PASI score of 125% of that at baseline, or the occurrence of new generalized pustular, erythrodermic, or more inflammatory psoriasis occurring [41]. The VAS and BSA will be assessed every week during the first 4 weeks and every 2 weeks in the follow-up period. The DLQI will be self-assessed by patients every 4 weeks throughout the trial. Laboratory reports will be also monitored until the last visit. TCM syndrome is one of the assessments which will be recorded before and after the auricular acupressure, as well as at the end of the follow-up period (Table 2).

**Table 1 Tab1:** Summary of measurement

Outcome	Measurement tool	Details
Primary outcome		
Relapse rate	Psoriasis Area and Severity Index (PASI) score	Relapse defined as losing 50% of the improvement obtained from treatment once the treatment is stopped
Secondary outcome		
Time to relapse	PASI score	Time domain between achieving at least 50% reduction in PASI score and losing 50% of the improvement obtained from treatment once the treatment is stopped.
Time to new onset	PASI score	Time domain between lesion clearing and recurrence
Rebound rate	PASI score	Rebound defined as a severe and sudden change in the severity of psoriasis that is significantly worse than before the treatment was initiated
PASI improvement rate	PASI score	PASI score is a tool used to measure the severity and extent of psoriasis. It takes a few minutes and experience to calculate it accurately. A representative area of psoriasis is selected for each body region. The intensity of redness, thickness, and scaling of the psoriasis is assessed as none (0), mild (1), moderate (2), severe (3), or very severe (4)
VAS	Visual analog scale (VAS)	VAS is the most common pain scale for quantification of endometriosis-related pain. We use VAS to evaluate the feeling of pruritus in participants during the treatment period
BSA	Body surface area (BSA)	BSA is a common measure in the medical field and part of the complete body size and composition profile
DLQI	Dermatology Life Quality Index (DLQI)	DLQI is a dermatology-specific quality of life instrument. It is a simple 10-question validated questionnaire. At present, the DLQI is the most frequently used instrument in studies of randomized controlled trials in dermatology

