The primary aim of the present study is to evaluate the control of psoriasis recurrence after auricular acupressure plus usual treatment in patients. The secondary aim is to evaluate the effect of the auricular acupressure plus usual treatment versus usual treatment alone on cutaneous symptom reduction at 4 weeks. We hypothesize that the combined treatment group will contain a higher proportion of patients who are better maintaining their recover status after achieving PASI-50, and who have a greater reduction in cutaneous symptoms at 4 weeks, compared with the usual treatment group. We are unable to find any previously published studies that addressed these questions. This study is one of the first trials to evaluate the effect of auricular acupressure on psoriasis. It may contribute to the aims described above when auricular acupressure is used in addition to medication.

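### Table 1 starts time to relapse at PASI-50 during treatment but allows the event only after treatment stops, so differences in response timing shift this secondary outcome even when relapse is identical

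*Protocol article*

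**What the plan says.** Three places in the Outcome section bear on this.

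- **Table 1, time to relapse:** "Time domain between achieving at least 50% reduction in PASI score and losing 50% of the improvement obtained from treatment", with the loss counted only after treatment has stopped. The start is a PASI-50 response and the end is a loss after treatment.
- **Secondary outcome measurements, running text:** "Time to relapse is defined as the time it takes to lose 50% of the improvement obtained from treatment". No start point is given; the reader is sent to Table 1.
- **Primary outcome measurement:** "Relapse is defined as losing 50% of the improvement obtained from treatment once the treatment is stopped". The event is again tied to the stop of treatment. The same paragraph, however, opens with "The primary outcome measure in the trial is relapse rate in the treatment period and follow-up period".

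PASI is rated at every visit. Both arms are treated for 4 weeks and followed for 12. Under the ointment section, application ends before week 4 only if PASI reaches 0. The auricular acupressure section has no such early stop.

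The Discussion gives the aim, "The primary aim of the present study is to evaluate the control of psoriasis recurrence after auricular acupressure plus usual treatment in patients", and the hypothesis that the combined arm will contain more patients "who have a greater reduction in cutaneous symptoms at 4 weeks, compared with the usual treatment group".

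**The concern.** An interval meant to describe how long remission lasts should not depend on how quickly the patient responded. Here it does. The clock starts at a response that can come early or late within treatment, and the event cannot be counted until treatment is over. The stretch between the two is event-free by definition and still adds to the time.

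The outcome therefore mixes speed of onset with durability. Among the secondary outcomes it is the one closest to the primary aim of controlling recurrence, so a longer time to relapse would naturally be read as support for that aim. Such a result could arise with no effect on recurrence at all.

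**Working it through.** **1. The identity.** Write W for the week of PASI-50, S for the week treatment stops and R for the week of relapse. Table 1's interval is

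T = R − W = (S − W) + (R − S).

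Only R − S describes relapse after treatment. S − W is a credit fixed by response speed. With S = 4 and weekly visits (stated for VAS and BSA, assumed here for PASI), W runs from 1 to 4 and the credit from 3 to 0 weeks. Two patients who both relapse at week 8 score 8 − 1 = 7 weeks and 8 − 4 = 4 weeks, although both relapsed 4 weeks after stopping.

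**2. The plan's own figure.** No figure is given for time to relapse. The sample size is used only to set the size of the simulation. For 82% versus 62% (pooled proportion 0.72), two-sided α = 0.05 and power 0.80:

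n = [1.960·√(2·0.72·0.28) + 0.842·√(0.82·0.18 + 0.62·0.38)]² / 0.20² ≈ 77.9, so 78 per group.

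The plan's 77 gives power 0.795, so it is reproduced to within one patient.

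**3. Simulation with identical relapse after treatment.**

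- From the protocol: 82% relapse; 12 weeks of follow-up; 2-weekly follow-up visits (stated for VAS and BSA); 77 per arm.
- Assumed: exponential relapse time after a week-4 stop; every patient reaches PASI-50; a log-rank test, which the protocol does not name; the PASI-50 timings.
- Relapse law A, 82% by 4 weeks off treatment: hazard −ln(0.18)/4 = 0.429 per week, median ln 2/0.429 = 1.6 weeks.
- Relapse law B, 82% by 12 weeks off treatment: hazard −ln(0.18)/12 = 0.143 per week, median 4.85 weeks.
- Example of timing: weeks 1–4 with probabilities 0.1/0.2/0.3/0.4 (mean 3.0) versus 0.4/0.3/0.2/0.1 (mean 2.0).

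Share of trials significant at two-sided 5% with no difference in relapse (1,000 to 1,500 trials per cell; ranges are across repeated runs):

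| Mean PASI-50 week | Law A | Law B |
|---|---|---|
| 3.0 vs 2.0 | 67% | 16–17% |
| 3.0 vs 2.25 | 44–45% | 12–13% |
| 3.0 vs 2.65 | 13–14% | 6–8% |
| 2.75 vs 2.25 | 21.5% | 8% |
| Equal timing | 5% | 5% |

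For 3.0 versus 2.0 weeks, the average median time to relapse is 4.0 versus 5.0 weeks under law A and 7.0 versus 8.0 under law B. Measured from a common origin, the same trials reject in about 4–7%. If everyone stops at week 4, randomisation as origin adds the same 4 weeks to each time, so the log-rank result equals that for time since stopping.

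**4. Sensitivity, 3.0 versus 2.25 weeks.** If 82% is reached by 8 weeks off treatment, the rate is 18%. If only 70% of patients respond (0.70 × 77 ≈ 54 per arm), it is 32%, 16% and 11% for 82% relapse by 4, 8 and 12 weeks.

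**5. Direction.** Suppose control patients reach PASI-50 at weeks 1–4 in 10/15/15/10% of cases. The mean week among responders is (0.10 + 0.30 + 0.45 + 0.40)/0.50 = 2.50. Suppose the other arm is identical but has a further 20% responding at week 4. Its mean is (1.25 + 0.80)/0.70 = 2.93. The better-responding arm then starts its clock later and receives the smaller credit.

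**The case against.** **The start and end may not mean this.** Table 1 does not say that the 50% reduction is the first one, whereas the text on time to new onset does use that qualifier. PASI-50 might be intended as a condition for entering the analysis. The opening sentence on the primary outcome also counts relapse during treatment, which would shrink the guaranteed event-free time. Both points stand as ambiguities. They do not remove the problem: first attainment is the ordinary reading of Table 1, and the start still depends on response speed even if on-treatment relapse counts.

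**The direction is not given.** A reader might infer that the definition necessarily favours acupressure. The documents do not support that. The Discussion hypothesises a larger reduction at week 4, not an earlier PASI-50, and the example in step 5 shows that a better arm can lose credit.

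**The larger rates are one end of a range.** A reader might take 45–67% as the expected false-positive rate. Those figures need fast relapse and a PASI-50 lead of 0.75 to 1 week. The sample size section takes 82% from 4 weeks of follow-up but applies it to a comparison at week 12, so slower relapse is equally open. It brings the same scenarios down to about 12–17%.

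**It is one secondary outcome, and PASI is recorded at every visit.** True. Time from another origin can be derived later, but the definition as stated is still the one that would be reported.

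**Conclusion.** The point holds as a defect in a stated definition, not as missing detail. On Table 1's wording, on-treatment time after PASI-50 is credited as remission, and a difference between arms in PASI-50 timing shifts time to relapse when post-treatment relapse is the same. The mechanism follows from the wording alone. The size rests on assumed PASI-50 timing, exponential relapse and a log-rank test: about 6–17% false positives under slow relapse and about 14–67% under fast relapse, against about 5% with a common origin. The sign is conditional on which arm reaches PASI-50 earlier among its responders.

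It would go too far to say that the primary relapse rate or the sample size is biased by this; neither uses the PASI-50 start date. The change should be made, but the trial's main comparison does not depend on it.

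**What to change.** - In Table 1 and the running text, measure time to relapse from randomisation in both arms, in the population used for the primary relapse rate, with a stated rule for patients who never reach PASI-50.
- Report time to first PASI-50 separately as a measure of onset.
- Do not treat the scheduled week-4 visit as an equivalent origin. Ointment may stop earlier at PASI 0, so a post-stop loss could fall before that visit.
- Reconcile the sentence that counts relapse in both the treatment and follow-up periods with the definition that requires treatment to have stopped.

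**Cost.** No new data are needed, because PASI is rated at every visit; the work is an amendment of wording. The article reports 154 of 180 patients recruited, so the definition could be settled before analysis. Reported times will no longer read directly as duration of response, and they may look less favourable to a faster-responding arm. A common origin also does not remove selection if the population is limited to patients who reached PASI-50, so the population should be stated alongside it.

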**Table 2 Tab2:**
[figure not shown]
Schedule for treatment and outcome measurements

*BSA* body surface area, *CM* Chinese medicine, *DLQI* Dermatology Life Quality Index, *PASI* Psoriasis Area and Severity Index, *SAS* Self-rating Anxiety Scale, *SDS* Self-rating Depression Scale, *VAS* visual analog scale

### Health economics

Economic evaluation will be carried out from the perspective of the Health Department of Guangdong Province, which will be in the form of a cost-utility analysis conducted using utility values obtained from the DLQI preference-based quality of life measure. DLQI is a dermatology-specific quality of life instrument for routine clinical use. It is a validated questionnaire with 10 simple questions. At present, the DLQI is the most frequently used instrument for evaluating the impact of skin disease and related treatment on the lives of patients. The DLQI will be measured at baseline and at 4 and 16 weeks for utility-based quality of life evaluation in this study. Resource use will include intervention costs, healthcare costs, and community service costs, which will be calculated for each trial participant. We will analyze an incremental cost-effectiveness ratio (ICER) of cost per patient by calculating the incremental mean difference in costs between the two trial arms and incremental difference in patient outcome after the follow-up.

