## Methods/design

### Study design

This study is a two-parallel arm, assessor-blinded, randomized controlled trial. The trial will be conducted by Guangdong Provincial Hospital of Chinese Medicine (GPHCM) and performed at two clinical research centers in China (Guangdong Provincial Hospital of Chinese Medicine and Guangzhou Red Cross Hospital) in accordance with the Declaration of Helsinki and the Guidelines for Good Clinical Practice.

This study will select patients with blood stasis syndrome on a TCM diagnosis based on a TCM syndrome differentiation standard [29, 30]. Eligible participants will be stratified by age and sex and randomly allocated in a 1:1 ratio to one of the treatment arms (the auricular acupressure plus calcipotriol betamethasone ointment group or the control calcipotriol betamethasone ointment group) and receive treatment for 4 weeks, with 12 weeks of follow-up (Fig. 2). The Standard Protocol Items: Recommendations for Interventional Trials (SPIRIT) checklist is provided in Additional file 1.

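### The cost-utility analysis calls the DLQI preference-based but names no value set or mapping, and it skips weeks 8 and 12 of a DLQI collected every 4 weeks

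*Protocol article*

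**What the plan says.** **Source of utilities.** The Health economics section commits to a "cost-utility analysis conducted using utility values obtained from the DLQI preference-based quality of life measure". It then describes the instrument: "DLQI is a dermatology-specific quality of life instrument for routine clinical use. It is a validated questionnaire with 10 simple questions". Table 1, under Secondary outcome measurements, says the same: "DLQI is a dermatology-specific quality of life instrument. It is a simple 10-question validated questionnaire". Neither place mentions preference weights, a value set or a conversion to utility. No separate utility instrument is listed among the outcomes.

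**Timing.** Health economics states: "The DLQI will be measured at baseline and at 4 and 16 weeks for utility-based quality of life evaluation in this study". Secondary outcome measurements states: "The DLQI will be self-assessed by patients every 4 weeks throughout the trial". Under Study design, patients "receive treatment for 4 weeks, with 12 weeks of follow-up", which makes 16 weeks in all.

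**The ratio.** "We will analyze an incremental cost-effectiveness ratio (ICER) of cost per patient" is how Health economics opens its definition. The sentence goes on to name the between-arm difference in mean cost and a difference in patient outcome at the end, without saying which outcome. The Abstract announces a cost-effectiveness analysis from a care-provider perspective. Health economics names a cost-utility analysis from the perspective of the provincial Health Department.

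**The concern.** A cost-utility analysis needs an effect expressed in utility: health states weighted by preference on a scale anchored at full health and death. A condition-specific questionnaire score does not become a utility by being called one. It needs a value set for its items or a mapping onto a utility scale. The article asserts the property and then describes an instrument without it, so a reader cannot tell what the effect unit would be.

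The time points raise a second issue. Treatment lasts at most 4 weeks, and relapse is defined as loss of improvement once treatment has stopped, so the period after week 4 is where the arms are expected to separate on the primary outcome. The Sample size section takes a control relapse rate of 82% after 4 weeks of treatment and 4 of follow-up, that is, by week 8. An evaluation with no measurement between weeks 4 and 16 draws a straight line across that period, although the outcomes section says the missing values are collected.

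At stake is the cost-effectiveness conclusion, which the Abstract lists among the aims of the trial.

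**Working it through.** **1. Is there a figure to reproduce?** No. The article gives no utility, QALY, cost or ICER. What can be checked is whether the passages fit together and what dropping two visits does.

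**2. Label against description.** The label is preference-based. The description, given twice, is a validated 10-question dermatology-specific questionnaire. Nothing in the article connects the two.

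**3. Visits.** Follow-up ends at 4 + 12 = 16 weeks. Every 4 weeks from baseline gives weeks 0, 4, 8, 12 and 16. Health economics uses weeks 0, 4 and 16. The omitted visits are weeks 8 and 12.

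**4. Trapezoid weights.** Let d(t) be the between-arm difference at week t, with d(0) = 0. Linear interpolation gives areas in difference-weeks:

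- five visits: A5 = 4d(4) + 4d(8) + 4d(12) + 2d(16)
- three visits: A3 = 8d(4) + 6d(16)
- A3 − A5 = 4 × {[d(4) + d(16)] − [d(8) + d(12)]}

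The three-visit version agrees with the five-visit version only if d(4) + d(16) = d(8) + d(12). It is too small if the difference is larger in the middle, and too large if it is larger at the ends.

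**5. Assumed profiles** (d is the size of the difference where it is present):

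| Between-arm difference | A5 | A3 | A3/A5 |
|---|---|---|---|
| Constant from week 4 | 14d | 14d | 1.00 |
| Declines linearly from d at week 4 to 0 at week 16 | 8d | 8d | 1.00 |
| None at week 4, then d at weeks 8, 12 and 16 | 10d | 6d | 0.60 |
| d at weeks 4, 8 and 12, none at week 16 | 12d | 8d | 0.67 |
| d at weeks 8 and 12 only | 8d | 0 | 0 |
| d at week 4 only | 4d | 8d | 2.00 |

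The third row is the 40% loss: 1 − 6/10 = 0.40. With the incremental cost held fixed, the ICER rises by 1/0.60 = 1.67. The factors are the same whether d is in utility units or DLQI points.

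**6. Absolute size, third row.** For an assumed d of 0.02 to 0.10 in utility, five visits give 10 × 0.02/52 = 0.0038 to 10 × 0.10/52 = 0.0192 QALY. Three visits give 6 × 0.02/52 = 0.0023 to 6 × 0.10/52 = 0.0115 QALY.

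**7. The ratio.** The sentence contains an incremental cost and an incremental outcome, so its structure is that of an ICER. It lacks a named outcome, and the phrase cost per patient describes a cost and not a ratio of cost to effect.

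**The case against.** **A mapping may exist.** The text says utilities are obtained from the DLQI, which does not exclude a mapping, and a condensed article may leave the mapping to the full protocol. This stands against the inference that raw DLQI scores will be used directly as utilities, or that the ICER is invalid. It does not rescue the label: the article does more than omit a step, since it attributes to the instrument a property that its own description does not support.

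**Weeks 0, 4 and 16 may be a deliberate subset.** They are baseline, end of treatment and end of follow-up, and the schedule in Table 2 is not shown. So the two passages need not contradict each other. What remains is an unexplained choice to ignore two assessments that the article says are collected.

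**The ICER sentence does give incremental cost and incremental outcome.** This is correct. Only the unnamed effect and the loose phrase remain.

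**The loss could be overstated.** A reader might turn the 82% and the assumed 20-point reduction (62%) into a hazard ratio of 0.564, assume control retention of 18%, 9% and 5% at weeks 8, 12 and 16, and obtain 1.74 gain-weeks with all visits against 0.81 with weeks 4 and 16 only, so that the ICER more than doubles. The document does not support this. The retention at weeks 12 and 16 is not in it. The hazard ratio treats both relapse rates as applying at one time, whereas the cited 82% is after 4 weeks of follow-up and the reduction is assumed for week 12. Full loss of the gain on relapse goes beyond the 50% in the definition. The scenario also allows no difference at week 4, although the Discussion hypothesises one. If the combined arm gains 20% more by week 4, the three-to-five-visit ratio in the same model rises to 0.84; at about 42% more it reaches 1.00.

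**Conclusion.** The point holds in two parts. First, the cost-utility analysis is not supported as written, because the DLQI is labelled preference-based while no value set, mapping or utility instrument is named. Second, restricting the utility evaluation to weeks 0, 4 and 16 discards collected information from the off-treatment window. The loss of information is certain; the bias is not. It is nil for a constant or linear difference after week 4, a 40% loss if the arms separate only after week 4 and then stay apart, and anywhere from a factor of 0 to 2 across the profiles shown.

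These factors assume an area under the curve by linear interpolation, which the article does not spell out, and 4-weekly assessment running from baseline to week 16. Three time points do not by themselves make an ICER invalid. The evaluation is not the primary outcome and is not in the list of secondary outcomes, so the trial's main result is unaffected.

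**What to change.** - Remove the preference-based label. Then either derive utilities through a named DLQI-to-utility mapping and carry its uncertainty into the ICER, or report incremental cost per DLQI point (or per relapse avoided) and do not call it cost-utility. The choice is the sponsor's.
- Use all 4-weekly DLQI assessments (weeks 0, 4, 8, 12 and 16) for the area under the curve.
- Replace cost per patient with incremental cost divided by a named incremental effect.
- Reconcile the form and perspective of the evaluation with the cost-effectiveness analysis announced in the Abstract.

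The change is to wording and analysis only, since the article already has the DLQI collected at these visits. Adding a utility instrument now is not a practical alternative: with 154 of 180 patients recruited, at most 26 (26/180 = 14%) could complete it from baseline. The downside is slightly more analysis work and, without a mapping, no QALY headline.

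### The economic evaluation is called a cost-utility analysis, but the ICER's stated unit and denominator do not make it a cost per QALY

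*Protocol article*

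**What the plan says.** All the relevant statements on the ratio stand in the Health economics section of the protocol article.

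- Type of evaluation: a "cost-utility analysis conducted using utility values obtained from the DLQI preference-based quality of life measure".
- Utility time points: "The DLQI will be measured at baseline and at 4 and 16 weeks for utility-based quality of life evaluation in this study".
- Costs: "Resource use will include intervention costs, healthcare costs, and community service costs, which will be calculated for each trial participant". No start or end of the costing period is given.
- The ratio: "We will analyze an incremental cost-effectiveness ratio (ICER) of cost per patient", calculated from the "incremental mean difference in costs between the two trial arms and incremental difference in patient outcome after the follow-up".

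The section does not say which patient outcome enters the ratio. Neither QALYs nor any accumulation of utility over time is named in the article. Under Study design, participants "receive treatment for 4 weeks, with 12 weeks of follow-up", so follow-up ends at week 16. Under Secondary outcome measurements, the DLQI is to be completed every 4 weeks throughout the trial, which is more often than the three time points named for the economic evaluation.

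**The concern.** A cost-utility ratio is an incremental cost per unit of utility-weighted time. Cost per patient is a mean cost and has no outcome in its denominator. The formula that follows does have an outcome, but on its plain reading it is the difference found once follow-up has ended.

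This matters because of where the trial expects benefit. The Discussion hypothesises that patients on combined treatment will better hold their improvement after PASI-50 and are also those "who have a greater reduction in cutaneous symptoms at 4 weeks". Both benefits arise between baseline and week 16. A contrast at week 16 counts them only as far as they are still present on that day, whereas acupressure is delivered, and its cost incurred, in the first 4 weeks. A treatment that improves week 4 and delays relapse, but is level with control by week 16, would have a denominator near zero and an undefined or very large ratio.

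Cost-effectiveness is one of the three things the Abstract says the trial will investigate. A ratio that is not a cost per QALY cannot be compared with a cost-per-QALY threshold.

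**Working it through.** The section states no cost, utility or ratio, so there is no figure of the plan's own to reproduce. The check is what the formula yields if its denominator is the week-16 utility difference. DLQI-derived utilities are taken as given.

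**Inputs from the document.** Utility at weeks 0, 4 and 16 (Health economics); 4 + 12 = 16 weeks in total (Study design).

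**Assumptions.** Between-arm utility difference 0 at baseline, d4 at week 4, d16 at week 16, linear in between. For the table, an incremental cost of 100 units.

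**QALY gain by the trapezoid rule**

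[4·(0 + d4)/2 + 12·(d4 + d16)/2]/52 = (8·d4 + 6·d16)/52

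**Comparison with d16 as denominator**

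- Constant benefit, d4 = d16 = d: the QALY gain is 14d/52 = 0.269d, so the week-16 ratio is 52/14 = 3.7 times lower than cost per QALY.
- The two agree when d16 = (8·d4 + 6·d16)/52, that is 46·d16 = 8·d4, or d4 = 5.75·d16. With d16 positive, the week-16 ratio is the higher one beyond that point.
- Scaling d16 by 16/52 years does not repair it: 16·d16 = 8·d4 + 6·d16 holds only when d4 = 1.25·d16.
- With d16 = 0, the QALY gain is 8·d4/52 = 0.154·d4, but the week-16 ratio is undefined.

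| d4 | d16 | QALY gain | Cost per QALY | Week-16 ratio | Week-16 ratio ÷ cost per QALY |
|---|---|---|---|---|---|
| 0.05 | 0.10 | 0.0192 | 5200 | 1000 | 0.19 |
| 0.05 | 0.05 | 0.0135 | 7429 | 2000 | 0.27 |
| 0.05 | 0.025 | 0.0106 | 9455 | 4000 | 0.42 |
| 0.05 | 0.005 | 0.0083 | 12093 | 20000 | 1.65 |
| 0.05 | −0.01 | 0.0065 | 15294 | −10000 | sign reversed |

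**Are weeks 0, 4 and 16 enough for the area?** Take the relapse proportions of the Sample size section, 82% and 62%. Assume they apply at week 8, with a constant relapse rate from week 4 to week 16, equal utility at week 4 and a utility loss d at relapse. The differences in the proportion still relapse-free are then:

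- week 4: 0
- week 8: 0.38 − 0.18 = 0.20
- week 12: 0.38² − 0.18² = 0.112
- week 16: 0.38³ − 0.18³ = 0.049

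Results:

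- Exact gain. Relapse rates are −ln(0.18)/4 = 0.4287 and −ln(0.38)/4 = 0.2419 per week. Mean relapse-free time is (1 − 0.0058)/0.4287 = 2.319 weeks and (1 − 0.0549)/0.2419 = 3.907 weeks. The difference of 1.588 weeks is 0.0305d QALY.
- Weeks 0, 4 and 16 only: 12 × 0.049/2 = 0.294 weeks = 0.0057d, less than a fifth of the exact gain.
- Every 4 weeks: 4 × [(0 + 0.20)/2 + (0.20 + 0.112)/2 + (0.112 + 0.049)/2] = 1.346 weeks = 0.0259d, about 85% of it.

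So the remedy should use all the four-weekly DLQI assessments.

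**The case against.** The strongest reply is that this is loose wording in a condensed article rather than a fixed wrong formula. The outcome is undefined, and the reference to after the follow-up may only say when the ratio will be computed. The section does call the evaluation cost-utility. It collects utility at week 4, for which a pure week-16 contrast has no use, and weeks 0, 4 and 16 would support an area-under-the-curve calculation. How QALYs are built is commonly left to a health-economic analysis plan, so silence on it is no finding.

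Most of this stands as a limit on the claim. A reader might infer that the plan definitely divides 16 weeks of costs by a week-16 snapshot and excludes quality-adjusted time. The text does not say so: the week-16 denominator is its plain reading but not its only one, and the 16-week cost window is an inference. A reader might also infer that the reported ratio will be wrong several-fold. That is not supported either, because every multiple above rests on assumed utilities. The multiples also compare cost per utility point with cost per QALY, so they describe an error only if the ratio is read as a cost per QALY.

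The reply does not rescue the sentence. The article goes beyond silence: it states a unit and a denominator. Even if the phrase only marks timing, cost per patient is not the unit of a cost-utility ratio and the outcome remains unnamed.

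**Conclusion.** The point holds in limited form. The stated unit is wrong for a cost-utility ratio, and the stated denominator, read literally, is an end-of-follow-up difference rather than utility accumulated over 16 weeks. The cost window is not stated.

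On the literal reading, the ratio could lie below or above cost per QALY. It is about 3.7 times lower for a constant benefit, higher once d4 exceeds 5.75·d16 with d16 positive, and opposite in sign if the week-16 difference reverses while the QALY gain stays positive. These figures assume no baseline difference and linear change between visits. They show that direction and size are open and do not predict this trial's result. The problem is confined to the economic evaluation; the primary outcome and sample size are unaffected.

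**What to change.** Replace the last sentence of the Health economics section with text to this effect: *The ICER will be the between-arm difference in mean cost over weeks 0–16 divided by the between-arm difference in mean QALYs over weeks 0–16. QALYs will be each participant's area under the utility curve, using all DLQI assessments planned every 4 weeks, and the difference will be adjusted for baseline utility. The result will be reported as cost per QALY gained.*

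Delete the cost-per-patient label, and align the utility time points in this section with the four-weekly DLQI schedule under Secondary outcome measurements. If the week-16 difference is kept, present it as descriptive only.

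This costs a short text change and slightly more computation. It needs no DLQI assessments beyond those already planned. The ratio may come out less favourable than one based on week 16 alone.
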